## Abstract

Sustainability of intervention programming is challenging to achieve under real world conditions, since few models exist and many studies do not plan far beyond the funding period. Programming content in early care and education centers (ECECs) is often driven by guidelines. However, implementation is very sensitive to contextual factors, such as the setting and implementer (teacher) characteristics. This paper presents the model, definitions, and methodology used for the sustainability action plan capitalizing on a community-based participatory research (CBPR) approach, developed for a multi-site, multi-level garden-based childhood obesity prevention study, Sustainability via Active Garden Education (SAGE). The Ecologic Model of Obesity is applied to develop a sustainability action plan (SAP) and accompanying measures to link early care and education (ECE) environment, the community, policies, and classroom practices to an early childhood obesity prevention program. The SAGE SAP provides an example of how to iteratively evaluate and refine sustainability processes for an obesity prevention intervention utilizing CBPR approaches and will be applied to assess the sustainability of SAGE in a cluster randomized controlled trial. This SAP model can also help inform intervention delivery and scalability within ECECs.

## 1. Introduction

Sustainability of health promotion programming is the concept that policies, programs, and practices can be maintained after an initial intervention period [1,2]. In the case of childhood obesity, effective intervention efforts currently exist [3,4,5]. However, sustaining program effects has been challenging, since the tightly-controlled laboratory conditions of success are not easily maintained or scalable [6,7,8]. Although a critical goal, sustainability is often difficult to attain due to lack of knowledge about the best processes, needed resources, and barriers and facilitators to program institutionalization [9,10,11,12,13]. Prospectively designing and evaluating strategies to improve sustainability are important as they can ensure that the methods used to sustain and disseminate project activities can be replicated [12,14].

In implementation science, approaches that are designed to improve the adoption, implementation, sustainment and/or dissemination of evidence-based interventions are called implementation strategies (hereafter referred to as strategies) [15,16,17]. Strategies can focus solely on one outcome (e.g., sustainment) or multiple outcomes (e.g., implementation and sustainment). They also may be discrete—containing a single component such as a teacher training—or multifaceted, including multiple discrete strategies (i.e., trainings, improving organizational processes, and providing resources) [16]. In short, strategies are all of the support and resources provided to help staff (e.g., teachers, directors) and sites (e.g., Early Care and Education Centers [ECECs]) deliver an intervention [18]. In recent years, researchers have been placing increased emphasis on naming the strategies used to deliver interventions, defining the strategies’ components, and operationalizing how each strategy will work [17], a process that also requires understanding of the broader context in which an intervention is delivered.

Focusing on the sustainability of an intervention is also key to reducing long-term health disparities [12]. Children who experience greater health disparities may live and attend ECECs and schools in contexts where there is even less support and fewer resources to sustain successful health promotion interventions. Sustainability planning is particularly important for improving the delivery of obesity prevention interventions with Hispanic preschool-aged children in the US. Hispanic children participate in less physical activity than their non-Hispanic peers and have higher rates of obesity, diabetes, and other chronic diseases [19,20,21,22,23]. There are also few evidence-based interventions for Hispanic preschool-aged children [24] that occur during the times when they are at ECECs [25]. Generally, school-based obesity prevention interventions have poor long-term effectiveness outcomes due to the numerous barriers and facilitators associated with maintaining the delivery of interventions in this setting [26]. Further, sustainable interventions must be replicable, institutionalized, demonstrate continued benefits, have a supportive community context, and be efficient to deliver [14,27]. Developing sustainability also necessitates significant community and organizational input and buy-in during the formative phases of the intervention [10]. Early buy-in can lead to the transfer of program impact beyond participants to other individuals or environments through linkages (i.e., child at ECEC to parent at home) [28,29], creating a “ripple effect” that is rarely documented or described in the literature [30].

The Ecologic Model of Physical Activity (EMPA) [28,29], which describes the levels and linkages related to physical activity behaviors, has also been applied to dietary habits and nutrition as the Ecologic Model of Obesity (EMO) [31,32]. The EMPA and EMO postulate that health-related behaviors and associated outcomes occur in a dynamic system with external contextual factors that influence individual behavioral choices and decisions directly and indirectly [28,29,31]. These external factors include children’s *micro-level* environments, such as ECECs and homes, their *meso-level* linkages, actors or activities within micro-level environments, such as teachers or family members, and *exo-level* linkages, actors or activities that transfer benefits to other people or places [33]. *Macro*-*level* factors might include societal and cultural norms or policies, as well as, community- and organization-level factors within children’s ecologic milieu. Understanding these contextual elements and improving the ones that influence implementation and sustainability of a childhood obesity intervention at an ECEC can result in carefully and consistently delivered interventions that are executed by motivated and capable individuals. In turn, these interventions can improve an organization’s ability to influence children’s health environments and behaviors. Capitalizing on a community-based participatory research (CBPR) process, the Sustainability Action Plan (SAP) was developed to accompany the Sustainability via Active Garden Education (SAGE) program, a garden-based physical activity and healthy eating intervention for children within ECECs [34,35,36]. The SAGE SAP aims to improve the delivery and long-term maintenance of SAGE. The SAGE SAP evaluation protocols also apply a multilevel framework to investigate ECEC factors that influence intervention sustainability at the teacher level, identify critical processes for improving sustainability at the organization level, and evaluate how a community partnership contributes to program success. The goals of this manuscript are (1) to describe the model and process of the SAGE SAP and (2) describe the evaluation plan for measuring the impact of the SAP on the sustainability of SAGE.

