## 2. Method

### 2.1. SAGE Overview and Design

SAGE uses a garden-based curriculum to increase physical activity and improve fruit and vegetable consumption in young children, age 3-to-5 years old, at 24 ECECs to help meet national policy guidelines for ECECs [35]. As previously described, SAGE follows the EMO framework and is implemented in ECECs focusing on *micro-level* environmental changes by installing a garden and working with center directors to guide evidence-based ECEC policy choices. At the *meso level*, teacher training and support is used to deliver an enhanced garden-based curriculum to meet *macro-level* ECEC standards for obesity prevention and early education. Parents are engaged using weekly newsletters linked to garden and classroom activities to enhance *exo-level* transfer of benefits [33].

SAGE includes active learning games and songs that use the plant life cycle as a metaphor for human development. Children and teachers complete garden maintenance and exploration time as a part of the curriculum and to promote garden sustainability. Other curricular activities include three science experiments, mindful eating exercises (“tummy mindfulness”) to sample new fruits and vegetables, and interactive discussion time to reinforce content. All activities are designed to align with National Association for the Education of Young Children (NAEYC) teaching standards.

Garden locations are selected with ECEC directors, maintenance staff, and teachers involved with the delivery of SAGE. If a garden exists already but is not used, efforts are made to breathe new life into the existing build or, if it is not well sited (e.g., inadequate or excessive sun exposure, inadequate drainage), to relocate it. SAGE gardens are sized to maximize access for young children (4’ × 6’) and built using inexpensive, and widely available materials (cinderblocks, soil, trellises). CAB members, teachers, and SAGE staff work together to build the garden. Planting seeds and seedlings is incorporated into the curriculum so that children can participate in this activity. See the garden build protocol in Supplementary File S1.

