Following the Childhood Obesity Research Demonstration Project (CORD) sustainability model SAGE’s participatory approach was used to develop the SAP to (1) enhance the potential for SAGE to be *replicable*—repeatable, adaptable or expandable, (2) improve the ongoing *continuation of* SAGE *benefits* from program effectiveness, (3) understand existing policy and organizational structures in order to enhance *institutionalization*, and (4) leverage and expand *community capacity* [2]. SAP processes occur before and during implementation, and the impact of the SAP is evaluated throughout the protocol using a mixed methods approach.

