*Teacher Training and Technical Support.* Another part of curriculum delivery that promotes sustainability is the use of a “see one, do one, teach one” teacher training method that has been used in health care delivery. The first 12 sessions will be led by the research team over six weeks, with teachers observing and assisting in SAGE delivery. Gradually, teachers will begin to lead portions of sessions during this time. Then, the 12 sessions can be repeated over a second six-week period and led by the teachers with assistance from the research team. Teachers will complete a 90-min training session prior to beginning implementation and a 30-min booster session about five weeks into implementation. Trainings focus on five PRIME principles that reinforce best practices for delivering SAGE: *P*romote positive experiences, *R*oom management, *I*mprovement directed reinforcement, *M*odeling appropriate behaviors, and *E*stablishing garden maintenance. On-demand technical support will be available throughout the study for ECECs and teachers who desire additional help.

*Action Planning Meetings with Directors.* Over the course of the SAGE program, research staff will meet three times for one hour with ECEC directors to develop a plan for institutionalizing SAGE and sustaining it beyond the funding period. ECEC directors will also complete assessments to evaluate resources, barriers, and facilitators for sustaining SAGE. In the first meeting, directors will complete a self-assessment of their ECEC, be given the opportunity to ask questions or voice concerns about SAGE, and prompted to think about long-term sustainability. In the second meeting, after they have more experience with SAGE, directors will review the results from their assessments, discuss how their results compare to other ECECs, and develop an action plan and set goals for improving low-scoring areas. Each action plan will be discussed with the CAB to identify community resources to support each ECEC director’s goals and provide feedback. In the final meeting of the semester, SAGE staff and directors will discuss progress towards achieving their goals, reevaluate and set new goals as needed, and complete assessments a second time.

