At this step, a booster training session will be conducted with teachers. The booster training is used to provide formalized technical assistance as teachers begin to become the primary implementers—switching from the “see one” phase to the “do one” phase of implementation. The booster training helps teachers consider the best processes to integrate SAGE within their teaching styles and existing curriculum. Reflective listening and brainstorming will be used to generate site- and teacher-specific modifications that might be needed for sustainable delivery of SAGE. Booster sessions will be informal, but generally structured around the sustainability of three pieces of the program: gardens, the tummy mindfulness and experiential eating taste tests, and the curriculum.

*SAP Step 4. Preparing for harvest: SAP implementation (weeks 5–10).* Representatives (director, staff, and teachers) from each ECEC will meet with the research team to review how their center fared on assessments. Weaknesses can be identified with strategies to overcome them, based on realistically considering timelines and priorities. Two or three goals will be set based on areas identified for improvement (e.g., improving center policies, sustaining funding, training staff). SAP implementation progress will be reviewed during CAB meetings, and the CAB suggests helpful community resources. The research team will communicate this information and connect ECEC staff to resources.

At the end of step 4 and the 12-week intervention, assessments will be collected to determine how the SAP affects outcomes. Information collected during this phase will be relayed back to the CAB and ECEC directors. The CAB, ECEC directors, and the scientific team will work together to modify SAGE curricular components and implementation protocols for subsequent cohorts of ECECs that receive the SAGE program.

*Step 5. Harvesting the fruit: Interpreting and disseminating findings*. The SAP rollout process continues for three cohorts, including data collection throughout. Information gleaned can inform changes to the SAP. By using a cross-over design, the organizational assessment, development, implementation, and evaluation of the SAP is repeated 6 times over 3 cohorts. Thus, there is the opportunity to develop a comprehensive and robust SAP if changes are needed.

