### 2.8. Director Assessments

The *Director Program Sustainability Survey* is based on an existing tool [40] and measures factors associated with program sustainability including ECEC administration, policies, and procedures. Specifically, questions focus on the type of ECEC (e.g., for-profit vs. non-profit), the number, types, processes, and rules for meals served at the ECEC; current physical activity and nutrition training offered to staff at the ECEC as well as future training needs; use of best practices for physical activity and nutrition at the ECEC as well as barriers/facilitators to using those practices; and ECEC directors’ communication with parents. Directors complete this survey prior to and following implementation of SAGE. The 38 questions on this survey consist of check-all that apply, multiple choice, fill in the blanks, and Likert-type scale questions. Responses from baseline to post-intervention will be compared to evaluate the impact of the SAP on outcomes.

The *Sustainability Needs Assessment* (SNA) is based on an existing tool [1] and completed by the ECEC director during SAGE week 3 and SAGE week 10. This assessment allows the director to rate the SAGE program on five RE-AIM dimensions: reach, efficacy, adoption, implementation, and maintenance [45]. Each RE-AIM dimension is evaluated using 6–10 questions (37 total), which are scored using a five-point Likert-type scale: (1) strongly disagree, (2) disagree, (3) neither agree or disagree, (4) agree, and (5) strongly agree. The SNA also investigates process factors associated with implementing the new program such as the perceived feasibility of the study design, the center setting, and the community environment (e.g., having the space and resources available to support the program). Responses from baseline to post-intervention will be compared to evaluate the impact of the SAP on SAGE’s perceived RE-AIM characteristics.

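### The article promises the impact of the Sustainability Action Plan itself, but the described design can estimate only the joint effect of SAGE plus the plan

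*Protocol article*

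**What the plan says.** Throughout, SAP means the Sustainability Action Plan, as in the article, not a statistical analysis plan.

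**Claims about the SAP alone**
- The Introduction gives as goal 2 to "describe the evaluation plan for measuring the impact of the SAP on the sustainability of SAGE".
- Section 2.1 says "SAP processes occur before and during implementation, and the impact of the SAP is evaluated throughout the protocol using a mixed methods approach".
- Section 2.3, Step 4, says that the assessments at the end of the 12 weeks will show how the SAP affects outcomes.
- Section 2.8, on the Director Program Sustainability Survey: "Responses from baseline to post-intervention will be compared to evaluate the impact of the SAP on outcomes". The Sustainability Needs Assessment (SNA) is treated the same way, for SAGE's perceived RE-AIM characteristics.

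**How the SAP is delivered**
- According to the Introduction it "was developed to accompany the Sustainability via Active Garden Education (SAGE) program".
- Section 2.3, Step 5: "By using a cross-over design, the organizational assessment, development, implementation, and evaluation of the SAP is repeated 6 times over 3 cohorts".
- Section 2.10 names two kinds of programming at a centre, SAGE Garden or Child Safety. No third condition appears.

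**Joint or neutral wording elsewhere**
- Section 2.10 attributes change in NAP SACC and PARA to the SAP and SAGE together.
- Section 2.6 describes change on the teacher survey only as related to the intervention.

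**The concern.** The statements in the first group are causal and specific to the SAP. To support them, some centre or period would need SAGE without the SAP, and the article describes none. A change in a director's answers could come from the garden, the curriculum, the SAP strategies or the passage of time, and the planned comparisons cannot tell these apart.

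The Abstract offers the SAP model to inform delivery and scalability in other centres. A reader who takes the SAP-only wording at face value could adopt the SAP for gains that belong to the whole package, or that would have occurred without it. A separate analysis plan cannot repair this, because it cannot create a contrast that the design lacks.

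**Working it through.** The article states no figure on this point, so there is none to reproduce. The check is whether separate SAGE and SAP effects can be estimated from the comparisons described.

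**1. Component overlap.** Section 2.1 presents these as SAGE: "teacher training and support is used to deliver an enhanced garden-based curriculum", weekly parent newsletters, and work with directors on centre policy. Section 2.2 lists teacher training and technical support, newsletters, and action planning meetings with directors as SAP strategies. The text draws no line between the two.

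**2. Consistency of the repeats.** 3 cohorts × 2 cross-over periods = 6, the number of SAP repeats stated. This fits the SAP running once each time SAGE runs.

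**3. Cross-over against Child Safety.** Columns are intercept, period, SAGE, SAP.
- SAGE first: (1, 0, 1, 1), then (1, 1, 0, 0)
- Child Safety first: (1, 0, 0, 0), then (1, 1, 1, 1)

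The last two columns are identical. The rank is 3 for 4 parameters, so only the sum of the SAGE and SAP effects is estimable.

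**4. Director Survey, before and after SAGE, no comparator stated.** Columns are intercept, SAGE, SAP, time.
- Before: (1, 0, 0, 0)
- After: (1, 1, 1, 1)

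The rank is 2 for 4 parameters. SAGE, SAP and time are all confounded.

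**5. SNA at SAGE weeks 3 and 10 (section 2.8 and Table 2).** Same columns.
- Week 3: (1, 1, 1, 0)
- Week 10: (1, 1, 1, 1)

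The rank is again 2. SAGE and SAP are on at both visits and only time changes. Section 2.8 calls this a comparison from baseline to post-intervention, but neither visit is a pre-SAGE or post-programme measurement.

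**6. Secondary check: areas chosen for low scores.** Section 2.2 has directors "develop an action plan and set goals for improving low-scoring areas", and section 2.3 adds: "Two or three goals will be set based on areas identified for improvement". Assessments are then repeated. With no true change, retest reliability r, and areas that are independent with equal means, the expected rise in the chosen areas is (1 − r) × c SD. Here c is the average distance of the chosen areas below the mean at first assessment. Taking the SNA's five dimensions, the simulation at r = 0.5 gives c = 0.415/0.5 = 0.83 for the lowest two and 0.277/0.5 = 0.55 for the lowest three.

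| Reliability (assumed) | Lowest 2 of 5 | Lowest 3 of 5 |
|---|---|---|
| 0.9 | 0.08 SD | 0.06 SD |
| 0.8 | 0.17 SD | 0.11 SD |
| 0.7 | 0.25 SD | 0.17 SD |
| 0.6 | 0.33 SD | 0.22 SD |
| 0.5 | 0.42 SD | 0.28 SD |

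The untargeted areas fall to match, and the mean over all areas changes by 0.00.

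**The case against.** **Bundling is by definition.** The Introduction defines implementation strategies as all the support given to help sites deliver an intervention. Training and newsletters under both headings follow from that, and the overlap is not itself an error. The Discussion describes the purpose more modestly, as a mixed-methods assessment of SAGE's potential for sustainability. This stands, but it supports a joint claim and not a SAP-only one.

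**Part of the SAP falls between the SNA visits.** The booster session (Step 3) and goal setting (Step 4) come after week 3, so week 3 to week 10 might seem to capture them. But SAGE sessions continue throughout, and their leadership passes from the research team to the teachers over the same weeks. Comparing successive versions of the SAP across cohorts does not help either: Step 4 allows SAGE's curricular components to be modified between cohorts as well.

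**Stronger readings that the article does not support**
- A reader might infer that all director, teacher and environment changes are credited to the SAP alone. Sections 2.6 and 2.10 show otherwise. The SAP-only comparisons are the two director instruments in section 2.8.
- A reader might infer that gains in low-scoring areas will be reported as impact and are inflated by regression to the mean. No such analysis is stated. Section 2.8 compares responses as a whole, where the effect cancels, and the goals given as examples in Step 4 are actions such as staff training.
- The size is not fixed either. With 24 items (the length of NAP SACC) the lowest two would rise 0.35 SD at reliability 0.8, about twice the 0.17 SD for five areas. The article does not say which instrument defines a low-scoring area.
- A reader might think that comparing targeted with untargeted areas isolates the SAP. It does not, because advisory board support, training, newsletters and the website reach untargeted areas too.

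**Conclusion.** The point holds for goal 2, the closing paragraph of section 2.1, Step 4 in section 2.3, and the Director Survey and SNA comparisons in section 2.8. As described, the SAP's own effect is not identified. At best the joint effect of SAGE plus SAP can be estimated, against Child Safety, for measures taken in both conditions. For the Director Survey even that is mixed with time, and the SNA shows only change during the programme.

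This rests on the article describing every condition in the trial; a SAGE-without-SAP condition set out elsewhere would change it. The conclusion concerns attribution, and no numerical bias follows from the article for the planned comparisons. Regression to the mean is a caution for goal-progress reporting only, and its size rests on a reliability and a number of areas that the article does not fix.

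**What to change.** 1. Reword goal 2, section 2.1, Step 4 and section 2.8 so that the effect is that of SAGE plus SAP, in line with section 2.10. The reference to the SAP's efficacy in section 2.4 should follow.
2. For measures taken in both conditions, such as NAP SACC, estimate the joint effect against Child Safety. Leave out Child Safety periods that follow SAGE, because the SAP is designed to make the programme persist and carry-over is therefore expected.
3. Report Director Survey changes as descriptive. Report the SNA as change from week 3 to week 10, without the baseline label. The SNA asks directors to rate SAGE itself, so Child Safety offers no reference for it.
4. If progress on areas chosen for low scores is reported, show untargeted areas beside it and note regression to the mean.

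The cost is mostly wording, with no new data collection. Dropping Child Safety periods after SAGE gives up some within-centre information and so some precision. The main downside is a more modest claim. Isolating the SAP would need a SAGE-without-SAP condition, which is a different trial.
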